**Trial registration number:**

ISRCTN17658526.

Strengths and limitations of this studyThe unruptured intracranial aneurysm (UIA) treatment rate is lower in the UK than in many other high-income countries, which reduces selection bias and allows observation of the true UIA natural history.The large cohort size will allow inclusion of more covariates in prediction models than has been possible in previous studies including rare, but salient, patient groups such as those with autosomal dominant polycystic kidney disease.The UK has uniform medical coverage and given virtually all patients who suffer subarachnoid haemorrhage seek medical help, the strategy to use national databases for hospital admissions and deaths in a defined population provides a robust method for identification of outcome events with minimal loss to follow-up.This design makes the Risk of Aneurysm Rupture study an order of magnitude larger than previous natural history studies and allows for repeated follow-up and generation of true long-term rupture risk.Identifying rupture events from hospital admissions databases is reliant on diagnosis coding accuracy; this limitation has been mitigated by searching a broad range of possible codes for intracranial haemorrhagic events and subsequent diagnosis verification against original imaging studies.

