Patient identifiable details (name, date of birth, post code, NHS/CHI number) will be securely sent by each neurosurgery unit to the coordinating centre for consolidation and linkage to the national databases for hospital admissions. These databases are: Hospital Episode Statistics (HES), Patient Episode Database for Wales (PEDW) and Scottish Morbidity Database (SMD). These databases also link to the Civil Registrations—Death and National Registry Scotland for death records. Patients will be linked to hospital admissions based on International Classification of Diseases 10th Revision (ICD-10) diagnosis codes for intracranial haemorrhages and OPCS4 codes for aneurysm occlusion treatments. These databases record every hospital admission in their respective country and thus using this as the outcome source, combined with death records, will allow identification of every aneurysmal subarachnoid haemorrhage (aSAH) regardless of whether they were managed in a neurosurgery unit, a district general hospital, migrated out of the region in which their UIA was diagnosed, or died in the community. The number of patients with aSAH who are not captured by this method, either because they do not present to hospital or emigrate out of the UK, is expected to be very small. Rupture rates can be adjusted based on national emigration rates.

Patients will be censored if there is any occlusive treatment of the UIA or patient death. Occlusive treatment includes either microsurgical or endovascular techniques either partial or complete. If none of these censoring events are observed, then they will be censored on the day the cohort is submitted to the HES/PEDW/SMD databases.

The ICD-10 codes to be searched for rupture events have been selected in accordance with the UK Biobank stroke research and include: aSAH (I60.1-9), intracerebral haemorrhage (I61.0-9), traumatic subarachnoid haemorrhage (S06.6) and spontaneous subdural haemorrhage (I62.00-I62.02).^16^ The use of codes beyond those for aSAH will capture any hospital admissions for aneurysm rupture which have resulted in other forms of intracranial bleed or have been miscoded.

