It is expected that the use of codes beyond that for just aSAH will return many admissions not due to aneurysm rupture. The matched hospital admissions, and death records, will be returned to the coordinating unit who will in turn use pseudonymisation numbers to inform the respective local unit of their patient’s admission for possible aSAH. The local unit will review the imaging studies, discharge summaries and death certificates for these admissions and confirm or refute the diagnosis. Statistical analysis will begin once the diagnosis for all of the matched admissions is confirmed.

The study is currently opening new sites and identifying patients for inclusion. The baseline data collection is planned to finish by 31 July 2023 and the results released no sooner than 31 July 2024. The study end date is currently 31 July 2034 to allow for repeated searching of hospital admissions databases in the future thereby further extending the follow-up period.

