One of the limitations of using national databases for hospital admissions is that identifying rupture events relies on the accuracy of the hospital coders and the diagnosis codes they assign (both to the primary and secondary diagnoses). The ROAR study will assess the magnitude of any miscoding by collecting any available follow-up data from the neurosciences record. In cases where a confirmed aneurysm rupture occurred, we will examine which hospital codes were assigned to that episode. We will also mitigate this limitation by searching for codes for all types of intra-cranial haemorrhage, not just subarachnoid haemorrhage, and subsequently review the medical records and imaging studies to confirm the true diagnosis for that patient.

While subject to a number of limitations, the ROAR study has mitigations for most of these and will therefore be less susceptible to them than previous studies. It is therefore expected to definitively evaluate the validity of PHASES, assess additional predictors of rupture and assess long term risks of rupture.

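### The printed rupture-code list starts at I60.1 and takes in only the subdural part of I62, which conflicts with the claims to search all intracranial haemorrhage codes and find every aSAH

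*Protocol article*

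**What the plan says.** All references are to the protocol article.

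- **Study design, code list.** The rupture codes "have been selected in accordance with the UK Biobank stroke research and include" the following: "aSAH (I60.1-9), intracerebral haemorrhage (I61.0-9), traumatic subarachnoid haemorrhage (S06.6) and spontaneous subdural haemorrhage (I62.00-I62.02". No other section adds I60.0 or any further I62 code.
- **Study design, completeness.** Using admissions databases together with death records "will allow identification of every aneurysmal subarachnoid haemorrhage (aSAH"). The only losses foreseen there are patients who do not present to hospital and patients who emigrate.
- **Discussion, breadth.** Miscoding is to be mitigated by "searching for codes for all types of intra-cranial haemorrhage, not just subarachnoid haemorrhage". The strengths and limitations list is weaker: "searching a broad range of possible codes for intracranial haemorrhagic events".
- **Study design, review.** "The matched hospital admissions, and death records, will be returned to the coordinating unit", which then asks the local unit to confirm or refute the diagnosis.
- **Study design, procedures.** Admissions are also linked on "OPCS4 codes for aneurysm occlusion treatments", and any occlusive treatment of the aneurysm is a censoring event.

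**The concern.** Rupture is the primary end point, and the linkage search is the main way it is found. Local review after matching removes false positives. It cannot recover an admission that the search did not return.

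I60.0 lies inside the category that the study labels aSAH, so a rupture correctly coded there falls outside the printed search. That differs from the limitation the article acknowledges, which is coders assigning the wrong code.

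Missed ruptures lower the observed rate while the PHASES prediction stays the same. Objective 1 would then lean towards the finding that PHASES over-predicts, or would hide under-prediction if that is the truth. Objectives 2 and 3 use the same events, and the planned repeat searches would carry the gap forward if they reuse the specification.

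**Working it through.** **1. The list against the claims**

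| Code group | Searched as printed | Not in the printed list |
|---|---|---|
| I60 (aSAH) | I60.1 to I60.9 | I60.0 |
| I61 (intracerebral) | I61.0 to I61.9 | none in the .0-.9 range |
| I62 | I62.00 to I62.02, subdural only | the rest of I62 |
| S06 | S06.6 | not at issue here |

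The gap in I60 conflicts with the claim to find every aSAH. The gaps in I60 and I62 both conflict with the Discussion's claim to cover all types.

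**2. What happens to a rupture coded only to an unlisted code**

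- *Another listed code on the same admission:* it is matched and reviewed.
- *Occlusion procedure on that admission:* it is linked on the procedure code. Occlusion is a censoring event, and the text does not say that a match on the procedure code alone is checked for rupture first. The event may be entered as a censoring.
- *Death:* death records are linked, and under Primary end points a certificate giving SAH in causes 1a-c counts as a rupture. The text does not say whether death records are searched on the same codes.
- *Local follow-up records:* the Discussion collects these where available, to measure miscoding. They are likely to be weakest for patients managed in district hospitals or who moved region, the groups for whom Study design relies on national linkage.
- *None of these:* the rupture is missed and the patient goes on contributing event-free time.

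**3. Illustration of size**

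Inputs from Sample size: 51 ruptures in 1692 patients over 4.1 years. The plan's own figures reproduce: 60 × 1692 / 51 = 1990.6 patients, and 1990.6 × 4.1 = 8161 patient-years (stated: 1990 and 8161). The planning rate is 51 / (1692 × 4.1) = 0.735 per 100 patient-years.

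Let f be the share of ruptures that carry only an unlisted code and that no other route finds. The article does not give f. The values below are assumptions, and f is 0 if the operative search already includes the codes. Observed rate = true rate × (1 − f).

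| f (assumed) | Observed rate per 100 patient-years | Events left of 60 (objective 1) | Events left of 120 (objective 2) |
|---|---|---|---|
| 0% | 0.735 | 60 | 120 |
| 5% | 0.698 | 57 | 114 |
| 10% | 0.662 | 54 | 108 |
| 20% | 0.588 | 48 | 96 |
| 30% | 0.515 | 42 | 84 |

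**4. Bias against precision**

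The article's ADPKD calculation implies 113 905 / 22 781 = 5 years per patient. At that follow-up, 20 000 patients give 20 000 × 5 × 0.00735 = about 735 events, before any person-time is lost to treatment. With f = 10%, about 662 are observed. A Poisson 95% interval is roughly ±1.96/√662 = ±7.6%, that is 0.662 × (1 ± 0.076) = 0.611 to 0.712, which excludes the true 0.735. With f = 5%, about 698 are observed and the interval is 0.698 × (1 ± 0.074) = 0.646 to 0.750, which includes it. The number of events is therefore not the problem. In a cohort this large, a modest loss can exceed sampling error.

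**The case against.** The best defence is that the list may not be the operative specification. It is introduced by a word meaning that the codes are among those searched, in an article that condenses a fuller protocol, and it is said to follow a cited source that is not shown. A range starting at .1 beside one starting at .0 may simply be a misprint. This stands as a reason for caution about the effect. It does not remove the point, because this is the only list given, it is presented as the search specification, and a misprint in it would need correcting too.

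The second defence is that other routes exist: co-listed codes, procedure codes, death records and local follow-up data. The Discussion also plans to examine which codes confirmed ruptures received, which could expose an omitted code. This stands as well. A reader might infer that ruptures under the unlisted codes can never reach review, and the article does not support that. The routes are partial, and one of them may turn an event into a censoring.

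A reader might go further and infer that the loss falls on one aneurysm site and biases its coefficient by a definable amount. The article does not say what anatomical site I60.0 denotes, gives no distribution of codes, and takes aneurysm characteristics from local baseline records, not from the rupture code. Nor does it say which unlisted I62 code a poorly coded rupture would receive, or how the databases store and match codes. Claims about site-specific bias, about particular I62 codes or about code length therefore have no footing here.

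Finally, the I62 conflict could be resolved by wording alone, since the strengths and limitations list claims only a broad range. That is fair for I62. It does not help with I60.0, which belongs to the target category.

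**Conclusion.** The point holds in a limited form. The printed list omits I60.0 and all of I62 except the subdural codes, and it contradicts two statements about completeness in the same article. Followed as written, it under-ascertains non-fatal ruptures coded only to those codes and may record some treated ruptures as censored. The direction is clear: the primary rupture rate is pushed down and PHASES appears to over-predict. The I60.0 gap matters more than the I62 gap.

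The size is unknown. The figures in the working rest on an assumed f of 5% to 30%, on the plan's ISUIA rate, on 5 years per patient and on no other route recovering the events. They show how a loss would translate into bias and are not an estimate of the loss.

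**What to change.** 1. Confirm the codes in the data request. State the SAH range as I60.0-I60.9, and list the I62 codes needed to support the claim of all types. If the narrower I62 search is intended, narrow the wording in Study design and the Discussion to match.
2. State that every admission matched on an occlusion procedure code is checked for rupture before the patient is censored.
3. State whether death records are searched on the same codes.
4. If a search has already been run on the printed list, rerun it for the added codes before analysis.

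The cost is a one-line change to the data request and some additional admissions for local units to review. The review process is already designed to expect many matches that are not ruptures.

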### Eligibility criteria

#### Inclusion

Age 18 years or older.Intracranial, intradural, unruptured aneurysm.Aneurysm confirmed on cranial angiogram - Computerised Tomography Angiogram (CTA)/ Magnetic Resonance Angiography (MRA)/ Digital Subtraction Angiography (DSA).Identification of UIA from records between 1 January 2006 and 31 December 2020.

#### Exclusion

Mycotic or vasculitic aneurysms.Aneurysm diagnosed on CT or MRI alone.Arterio-Venous Malformation (AVM) associated flow aneurysms.Extradural aneurysms (eg, intracavernous).Aneurysms treated by either microsurgical or endovascular techniques before the search period.Small lesions uncertain as to whether they are truly aneurysmal (‘dilatation’, ‘bulge’, ‘infundibulum’).

### Outcomes

#### Primary end points

The primary end point is rupture of an untreated UIA at a timepoint at least 1 day following diagnosis. A rupture event is defined as either radiological evidence of aSAH in a distribution consistent with the aneurysm location, CSF spectrophotometry positive for xanthochromia per the local unit’s reference range or death certificate stating subarachnoid haemorrhage in causes of death 1a-c.

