### Study design

The Risk of Aneurysm Rupture (ROAR) study is a longitudinal study that uses a hybrid design of patient identification at regional neurosurgical units and prospectively collected national hospital admissions databases for outcome events. The study will establish a cohort of patients with a UIA and measure how many subsequently ruptured. This observed rupture rate can be compared with a rate estimated by the PHASES score to determine its accuracy.

Each neurosurgery unit in the UK will be invited to search their medical records for patients diagnosed with a UIA. This search method will be tailored by the individual neurosurgery unit based on what records they keep, but search strategies may include: multidisciplinary team (MDT) meeting logs, radiology reports or electronic patient records. The search strategy will be predefined by individual units dependent on their record systems. The maximum date range for identifying patients is documents dated 1 January 2006 to 31 December 2020, however, this period may be shorter for each unit depending on availability of records. Whatever date range is chosen by the unit, it will be predefined and if the patient’s UIA was newly diagnosed during this period it will be classed as *new* and those who were diagnosed before this period but identified from a document during the aneurysm follow-up will be classed as *follow-up*, and their recruitment date recorded as the date of the document from which they were identified. This will minimise the prevalence-incidence (Neyman)^14^ selection bias created by identifying patients diagnosed before the unit’s search period but who survive without rupture to make it into the search period, whereas their counterparts diagnosed at the same time who rupture and die are not identified. It will also allow comparison of rupture risk of newly diagnosed aneurysms and those with known diagnoses. Baseline clinical characteristics and aneurysm characteristics will be collected as per the common data elements for UIA research.^15^ All data collectors will undergo training in coding data elements delivered by the coordinating centre. Collecting baseline data from local medical records allows deeper phenotypic typing and higher data fidelity than using national admission databases.

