## Discussion

Although the natural history of UIA has been previously investigated with multiple prospective cohort studies, the rupture rate has varied significantly between these. The design of the ROAR study addresses many of the criticisms of these previous natural history studies. ISUIA^7^ is the first natural history study and is drawn from a population that is genetically closest to that of the UK. However, its results are subject to selection bias with 71% of their UIA being treated either before inclusion or during follow-up. It is not known if that selection was random or based on a feature associated with risk such as aneurysm irregularity. It is therefore not known how the rupture rates in the remaining potentially lower-risk patients translate to the general population. The UK has a much lower treatment rate of UIA (approximately 20%). This is one of the lowest rates in a high-income country making it the ideal setting for a natural history study. It remains however that there will be some treatments performed during the study which inevitably will produce some selection bias that cannot be eliminated. Other countries with lower treatment rates are likely to also have low availability of imaging and hence much lower case identification limiting the cohort size and introducing different biases.

There is also a risk of selection bias in ROAR arising from the methods employed for patient identification. Patients in whom no MDT, clinic notes or radiology report was created would be effectively excluded. These are also the patients more likely to not undergo treatment. However, our survey of UK neurovascular surgeons suggest it is only a very small minority that are not discussed at MDT or seen in a neurosciences clinic. This was also borne out in pilot studies in the development of the protocol. The timeframe for searching patients within a unit’s available records creates the potential for introducing prevalence-incidence selection bias. The ROAR study will mitigate this by identifying patients as *new* or *follow-up* based on whether or not the UIA was diagnosed during that unit’s search window and use the identifying document dates accordingly.

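### No rule requires the identifying record or the confirming angiogram to predate rupture, so a rupture can bring its own patient into the cohort

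*Protocol article*

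**What the plan says.** All references are to the Protocol article.

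- **Primary end points:** "The primary end point is rupture of an untreated UIA at a timepoint at least 1 day following diagnosis". The clock for the event is diagnosis. Recruitment, the identifying document and the angiogram are not mentioned.
- **Inclusion:** "Identification of UIA from records between 1 January 2006 and 31 December 2020" and "Aneurysm confirmed on cranial angiogram" (CTA, MRA or DSA). Neither condition is ordered in time against rupture. The aneurysm must be unruptured, but the date at which this is judged is not given.
- **Exclusion:** "Aneurysm diagnosed on CT or MRI alone" and "Small lesions uncertain as to whether they are truly aneurysmal". Nothing says which scan decides these.
- **Study design:** each unit chooses its sources (MDT logs, radiology reports, electronic records). Records generated by a rupture are not ruled out. Patients diagnosed before the unit's window but found from a document during follow-up are classed as *follow-up*, with "their recruitment date recorded as the date of the document from which they were identified". No matching rule is given for *new* patients.
- **Study setting:** patients are identified by the unit that diagnosed the aneurysm.
- **Discussion:** "Patients in whom no MDT, clinic notes or radiology report was created would be effectively excluded". A survey and pilot work are cited to say that very few patients are missed, without a figure.

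**The concern.** Many ruptures will already have happened when a unit decides who enters. Take a patient whose aneurysm was diagnosed by angiogram at the unit within its window, but who does not appear in the source that the unit later searches. If the aneurysm ruptures, the admission creates an MDT entry and an imaging report. The search finds these, the diagnosis is more than a day old, and the event counts. If it does not rupture, no such record arises and the patient is never found. Entry then depends on the outcome.

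The article guards carefully against the opposite error, in which ruptured patients are lost: it addresses prevalence-incidence bias in Study design and consent bias in Ethical considerations. It does not discuss ruptured patients being preferentially captured.

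Objective 1 compares absolute observed 5-year risk with the PHASES prediction, so any inflation passes straight into calibration and makes PHASES appear to under-predict. The absolute risks in Objective 2 and the long-term rates in Objective 3 inherit it too. A larger cohort does not reduce it.

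**Working it through.** **Step 1: the passages side by side.**

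- *New* patients: the diagnosis must fall in the unit's window and the rupture at least 1 day later. No rule places the identifying document before the rupture.
- *Follow-up* patients: recruitment is the document date, but the end point runs from diagnosis. Read literally, a rupture after diagnosis and on or before recruitment satisfies the end point. The two sections need reconciling.
- Angiogram: required, but not expressly before rupture.

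**Step 2: the plan's own rate.** Sample size gives 51 ruptures in 1692 patients over 4.1 years in ISUIA.

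- Rate λ = 51 / (1692 × 4.1) = 0.735 per 100 patient-years.
- Patients for 60 events: 60/51 × 1692 = 1990.6. Follow-up: × 4.1 = 8161 years. Both match the stated 1990 and 8161.

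**Step 3: size of the mechanism.** The documents give no figure, so the inputs below are assumptions unless a source is named.

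- N = 20 000 properly entered patients (the target).
- T = 5 years each (the ratio 113 905 / 22 781 in Sample size).
- Constant hazard, the same in found and unfound patients.
- m = share of diagnosed aneurysms with no qualifying record before rupture.
- q = share of the ruptures in that group that enter through rupture-generated records.

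Formulas:

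- 5-year risk p = 1 − exp(−λT) = 3.61%.
- Events = N·p = 722. Person-time = N·p/λ = 98 184 years.
- Extra events = q · N·m/(1 − m) · p.
- Mean time to rupture given rupture within T = 1/λ − T·exp(−λT)/p = 2.48 years.
- Observed rate = (events + extra) / (person-time + extra × 2.48).

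Example, m = 5%, q = 1: the unfound group is 20 000 × 0.05/0.95 = 1053 patients, with 38 extra events. The observed rate is (722 + 38) / (98 184 + 94) = 0.773 per 100 patient-years, a factor of 1.052.

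| m | q | Extra events | Observed rate per 100 patient-years | Factor |
|---|---|---|---|---|
| 2% | 0.5 | 7 | 0.743 | 1.010 |
| 2% | 1 | 15 | 0.750 | 1.020 |
| 5% | 0.5 | 19 | 0.754 | 1.026 |
| 5% | 1 | 38 | 0.773 | 1.052 |
| 10% | 1 | 80 | 0.815 | 1.109 |
| 20% | 1 | 180 | 0.915 | 1.244 |

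At the 1.4% per year cited in the Introduction, or at the feasibility rate, the factors agree to within 0.005.

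**Step 4: scale.** With 722 events the relative 95% sampling half-width of the overall rate is about 1.96/√722 = 7.3%. Inflation of 1% to 5% lies inside that; 10% or more would not.

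**Step 5: do the feasibility data show it?** The rate is 60/4010 = 1.50 per 100 patient-years (exact 95% CI 1.14 to 1.93). That is 2.04 times the ISUIA rate, but only 60/56.1 = 1.07 times what 1.4% per year predicts. The data are compatible with some inflation and do not demonstrate it.

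**The case against.** The strongest reply is that the rules, read together, already imply the right order. The aneurysm must be unruptured, the study measures how many later rupture, and the diagnosing unit does the identifying. A *follow-up* document must arise during follow-up. The Discussion says that few patients escape both MDT and clinic. This is also a journal article, and date checks may sit in the full protocol.

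Much of this stands. The intent is clear, the diagnosing-unit rule narrows the route for patients never referred, and the Discussion points to a small effect. But none of these statements dates the identifying document, and the mismatch between recruitment date and end point is in the article's own text. The reassurance also covers MDT and clinic together, whereas a unit may search only one kind of record.

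A reader might go further and infer that an aneurysm seen only on plain MRI, or an uncertain bulge, enters as an event once the rupture angiogram proves it. The documents do not support that as it stands. If diagnosis is the MRI, the exclusion applies. If diagnosis needs the angiogram, it falls at the bleed, and the 1-day rule would ordinarily remove the event. The same holds for a lesion first proven aneurysmal by bleeding. These routes open only if diagnosis is dated from one scan and eligibility judged on another, which no section instructs.

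**Conclusion.** The point holds in a limited form. Followed literally, the end point and entry rules allow a patient with a previously diagnosed aneurysm to enter through a record created by the rupture, and this mechanism acts upward on rupture rates. Its size is unknown. It is probably small if the Discussion's description of missed patients is right: about 1% to 5% inflation if 2% to 5% of diagnosed aneurysms lack a qualifying record before rupture. Those shares, the constant hazard and the equal risk in found and unfound patients are all assumptions.

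A reader might infer that the study's rupture rates will be too high overall, or that the feasibility rate, at twice the ISUIA rate, proves it. Neither follows. Other selection effects may act downward, the net bias cannot be derived from the text, and the feasibility rate is close to the 1.4% per year that the article cites.

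**What to change.** 1. State in the eligibility criteria that the confirming angiogram and the identifying document must both predate any rupture of that aneurysm, and that the imaging exclusions are judged on pre-rupture imaging.
2. Start follow-up, as delayed entry, at the latest of diagnosis, confirming angiogram and identifying-document date, for *new* and *follow-up* patients alike. Keep time from diagnosis as the time scale where an objective needs it.
3. Count only ruptures at least 1 day after that entry date.
4. Tabulate the patients identified only from rupture-generated records and leave them out of the rates.

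Items 2 and 3 must go together. Moving the end point without moving the start of follow-up would leave the time from diagnosis to document in the denominator, although no event could count in it. That immortal time would bias rates downward.

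The cost is a small loss of counted events and early person-time, plus a date check on fields that sites should already hold. It is best settled during data collection: sites decide eligibility, and the analysis cannot repair it later unless these dates are captured.
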